### Self-reported outcomes

The primary outcome measure is IBD-related quality of life and this will be assessed using the Short IBD Questionnaire (SIBDQ) [35]. The SIBDQ consists of 10 items and measures the impact of IBD on social, emotional, systemic, and bowel well-being. The SIBDQ score ranges from 10 to 70 with higher scores representing better IBD-related quality of life. The SIBDQ is reliable and responsive to clinically meaningful change [36, 37]. Secondary outcome measures include the Patient Health Questionnaire-9 (PHQ-9), which is a reliable measure of the severity of depressive symptoms [38]. The PHQ-9 consists of 9 items and higher scores reflect higher levels of depressive symptoms. Sleep quality will be assessed using the PROMIS Sleep Disturbance Short-Form 8b, which is a reliable measure of sleep quality [39]. Higher scores on the PROMIS Sleep Disturbance Short-Form 8b reflect worse sleep quality.

### Clinician-rated outcomes

Clinician-rated disease activity will be assessed with the Harvey Bradshaw Index (HBI) for participants with Crohn’s disease or the Simple Clinical Colitis Activity Index (SCCAI) for participants with ulcerative colitis or IBD-unclassified [40, 41]. The HBI addresses general well-being, abdominal pain, liquidity of stool, presence of an abdominal mass, and complications, and must be completed in-person to conduct an abdominal examination. The SCCAI addresses bowel frequency, defecation urgency, blood in stool, general well-being, and extracolonic disease characteristics and can be completed in-person or remotely via video communication services.

### Exploratory outcome

We will assess for gastrointestinal inflammation by measuring fecal calprotectin. Fecal calprotectin is an inflammatory biomarker found in stool that is produced by neutrophils that infiltrate the colon and is more sensitive and specific for intestinal inflammation than systemic biomarkers derived from blood [42, 43]. Research participants will collect 1–5 gram stool samples at home the day before visit 3 (pre-treatment) and visit 7 (post-treatment). and deliver them to the study team during the study visits. The University of Michigan Central Labs will assay the samples using the commercially available INova QUANTA Flash Calprotectin Chemiluminescent Immunoassay. Participants will also complete Crohn’s disease and ulcerative colitis specific patient reported outcomes (CD-PRO and UC-PRO) that assess bowel symptoms, abdominal symptoms, systemic symptoms, daily life impact, emotional impact, and use of coping strategies [44, 45]. The CD-PRO and UC-PRO were developed in accordance with U.S. Food and Drug Administration Guidelines for use in clinical trials.

### Additional measures

At visit 2, participants will complete the Cambridge-Hopkins questionnaire [46] to screen for restless leg syndrome (RLS) which is present in 20–30% of patients with IBD [29–31]. For those that screen positive, the severity of RLS will be determined with the validated patient-report International Restless Leg Syndrome study group severity rating scale [47]. This scale assesses symptoms over the past 7 days and the total score ranges from 0 (no symptoms) to 40 (very severe symptoms). Patients who do not screen positive will be assigned a severity score of 0. The severity score will be used as a moderator in the statistical analysis (see below).

Participants will also complete several questionnaires at pre-treatment (visit 3) and post-treatment (visit 7). The Morningness-Eveningness Questionnaire (MEQ) [48] will be used as a proxy marker of circadian timing. The MEQ score correlates well with the gold standard circadian phase marker, the dim light melatonin onset, and significantly increases towards more morningness after 13–28 days of a morning light treatment [49]. This will allow us to confirm an expected phase advance or earlier shift in circadian timing in response to morning light treatment. Fatigue will be assessed with the PROMIS Fatigue Scale, where higher scores reflect more fatigue [50, 51]. Anxiety will be assessed with the PROMIS Anxiety Scale to measure anxiety, where higher scores reflect more anxiety [52, 53]. Finally, participants will also complete a brief questionnaire about their study expectations at visit 3 after they are informed of the condition they have been randomized to, and a study satisfaction questionnaire at visit 7.

Participants will wear the Fitbit Charge 5™ on their non-dominant wrist to monitor activity and sleep. The Fitbit Charge 5™ uses accelerometry and cardiac autonomic signals to estimate sleep and has been compared to gold-standard polysomnography, demonstrating differentiation of sleep and wake states superior to US Food and Drug Administration cleared actigraphy [54]. We will export data from the Fitbit Charge 5™ in 30 s intervals using Fitabase software. To augment the sleep data collected by the Fitbit device, sleep diaries will be completed, and participants will text a research email account to identify when they are trying to fall asleep (bedtime) and at their final wake time. Bedtime and rise time data through the time stamped text messages will allow for confirmation of correct sleep onset and offset and calculation of time in bed (TIB), total sleep time (TST), wake after sleep onset (WASO), and sleep efficiency (SE). These objective sleep parameters will be primarily used to verify participant adherence to the morning light treatment but will also be examined for group differences. Participants will also track their daily use of alcohol, caffeine, nicotine, medications, exercise, psychotherapy, and food timing on a daily event log.

### Safety measures

At each weekly visit after the start of treatment (visits 4–7), participants will complete a self-reported measure of physical and emotional symptoms they have experienced in the past week using the Systematic Assessment for Treatment Emergent Events (SAFTEE) as used in a previous light treatment study [55]. Unblinded research staff assess the severity of symptoms and their relevance to the study and assigned group, to ensure no significant negative effects are associated with the study participation. If severity meets a pre-determined threshold based on SAFTEE, the unblinded research staff alerts an unblinded study physician to further assess the participant’s safety and risk for an adverse event. In addition, at visits 4–7, suicidality will be assessed using the Columbia Suicide Severity Rating Scale (C-SSRS) [56], and mood worsening will examined with the Beck Depression Inventory [57]. 

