There is evidence that circadian disruption (disruption of the “body clock”) is present in IBD and is associated with worse disease activity and symptoms. A summary of the literature examining the influence of circadian factors on IBD-related outcomes in tissue, rodent, and human models is summarized in Table 1. This body of research suggests that circadian disruption may be an important modifiable treatment target in patients with IBD. As light is the strongest environmental signal affecting circadian timing [18], morning light treatment in combination with a regularly timed sleep schedule is a key approach to reducing circadian disruption in humans. Morning light treatment can phase advance (shift earlier) circadian timing, and when administered around habitual wake time will usually phase advance circadian timing by ~ 1 h [19, 20]. In addition to reducing circadian disruption, meta-analyses have confirmed that morning light treatment improves mood (reduces nonseasonal depression) with medium effect sizes similar to those observed with pharmacological antidepressants [21, 22]. Similarly, a meta-analysis indicates that morning light treatment improves sleep with medium effect sizes [23]. Importantly, while light treatment is associated with some side effects (headache, eyestrain, nausea, agitation [24]), these often spontaneously remit [24, 25], and patients rarely discontinue treatment due to side effects [25]. Furthermore, light devices (with UV filter) are considered safe with no changes in ophthalmologic exams observed after 6 years of daily use (in fall and winter months) [26]. Thus, morning light treatment, a treatment that can reduce circadian disruption, has potential to enhance usual treatment and improve symptoms and disease activity in IBD with minimal side effects. Furthermore, light treatment devices are commercially available and light treatment can be self-administered at home, allowing easy access and dissemination once efficacy is established.

**Table 1 Tab1:** A summary of the literature exploring circadian factors in IBD-related models

Model	Reference	Circadian Factor	Summary of Findings
Tissue	Palmieri et al. 2015; [60] Weintraub et al., 2020; [61] Liu et al. 2017 [62]; Mosna et al. 2021[63]	Clock gene expression in colonic mucosa, leukocytes	Altered expression in IBD and in inflamed mucosa, associated with increased endoscopic disease activity, inflammation

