### Study population

We aim to enroll 68 individuals with a biopsy-proven diagnosis of IBD, aged 18 years or older, who meet criteria for impaired IBD-related quality of life and report recent abdominal pain or bowel symptoms (Table 2). Impaired IBD-related quality of life will be reflected by a Short IBD questionnaire (SIBDQ) score < 60. We have chosen inclusion/exclusion criteria to permit as many people with symptomatic IBD as possible to participate safely, while maximizing generalizability of findings (Table 2). For example, prescribed hypnotics, over-the-counter sleep aids, and antidepressants will be permitted as their use is common in IBD, but these permitted medications will need to be stable for 30 days before and during the study. Changes in medications to treat IBD during follow-up will be permitted as this is typical in clinical practice (although changes in corticosteroids will be cause for exclusion due to impact on sleep quality which could confound study results, see Table 2). Participants will be able to continue psychological therapy, physical therapy, and exercise if the treatment was started 30 days prior to enrollment and continues during the study period. Participants must be physically able to travel for the study visits and have no experience with light treatment in the past year. Participation will be scheduled ≥ 1 month from night work, travel outside the eastern time zone, other research participation, and will be scheduled during a period with minimal special events (e.g., weddings, concerts, exams).

**Table 2 Tab2:** Inclusion and exclusion criteria

Inclusion criteria
1. Age ≥ 18 years old
2. Biopsy-proven IBD
3. Impaired quality of life: Short IBD Questionnaire (SIBDQ) < 60
4. Symptoms: at least “some of the time” abdominal pain or bowel symptoms on SIBDQ
5. Fluent in English
6. Physically able to travel to study visits, within 1.5 h drive of study location

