***Safety measures***								
BDI			X	X	X	X	X	X
C-SSRS (past 6 months)		X						
C-SSRS (since last visit)			X	X	X	X	X	X
SAFTEE					X	X	X	X

Eligible participants will be enrolled in the study at visit 2, during which some questionnaires to characterize the sample will be completed (Table 3). Participants will be given a Fitbit Charge 5™ to wear on their nondominant wrist to track their sleep and activity throughout the study protocol, along with daily logs to report their subjective experience of sleep and alcohol, drug, and medication use. One week later, at visit 3, pre-treatment outcome assessments will be administered, and participants will be randomized to the morning light treatment or TAU group (see below for more details). Treatment expectations will also be assessed at visit 3. Morning light treatment (or TAU) will then begin the morning after visit 3. Thereafter, there will be weekly visits (visits 4, 5, 6) to review each participant’s adherence to instructions (sleep timing and use of the Re-timer® in the morning light treatment group) and to systematically assess side effects (both groups). At visit 7, post-treatment outcome assessments will be administered, and study satisfaction will be assessed. Participants will be required to abstain from alcohol use within 24 h of visits, and to ensure compliance participants will be breathalyzed at the beginning of each visit.

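### SAFTEE is not given before treatment, so new or worsened symptoms cannot be identified per participant; what remains is a between-arm comparison of symptom prevalence, unbiased but diluted by background symptoms

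*Protocol article*

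**What the plan says.** The Safety measures section schedules SAFTEE "At each weekly visit after the start of treatment (visits 4–7". At those visits "participants will complete a self-reported measure of physical and emotional symptoms they have experienced in the past week". Table 3 matches: SAFTEE is marked at visits 4, 5, 6 and 7 and is blank at screening and visits 1 to 3.

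The Procedures and assessments section fixes the start of treatment: "Morning light treatment (or TAU) will then begin the morning after visit 3". Visit 3 is thus the last visit before treatment. The same section says that the weekly visits serve "to systematically assess side effects (both groups", so TAU is assessed on the same schedule.

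Inclusion criterion 4 in Table 2 reads "Symptoms: at least “some of the time” abdominal pain or bowel symptoms on SIBDQ". The Background acknowledges that "while light treatment is associated with some side effects (headache, eyestrain, nausea, agitation [24".

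Under Safety measures, unblinded staff judge how severe the symptoms are and how they relate to the study and the assigned group.

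The other two safety scales do have pre-treatment values in Table 3: BDI from visit 2 and C-SSRS from visit 1.

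**The concern.** As described, SAFTEE asks what the participant felt in the past week, not what has changed since treatment began. Everyone enrolled has some symptoms at entry. The Background section puts poor sleep at an estimated 56% of IBD patients and depression at 20–30% or more. An on-treatment report therefore mixes symptoms that were already there with symptoms that began or worsened on treatment, and the form holds nothing earlier to compare it with.

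Two things are at stake. First, a raw side-effect rate in the light arm would describe prevalence, not emergence. Second, the arm difference that remains is harder to detect, because participants who already had the symptom add noise and cannot show new onset. The trial is meant to inform a larger confirmatory trial on acceptability and feasibility, and tolerability data are part of that.

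**Working it through.** **1. Is there a pre-treatment SAFTEE?** The text gives visits 4–7, Table 3 gives visits 4–7, and treatment begins the morning after visit 3. The three agree, and there is none. The schedule is stated in two places, so this is not a detail left to a fuller document.

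**2. Does another instrument supply the missing baseline?**

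| Symptom domain | Pre-treatment measure in the protocol |
|---|---|
| Abdominal and bowel | SIBDQ, HBI or SCCAI at visit 3 (Table 3) |
| Mood | PHQ-9 at visit 3; BDI at visits 2 and 3 (Table 3) |
| Sleep | PROMIS Sleep Disturbance at visit 3 (Table 3) |
| Fatigue, anxiety | PROMIS scales at visit 3 (Additional measures) |
| Agitation | Partly approached by the anxiety scale |
| Headache, eyestrain, nausea | None described |

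These scales do not map item by item to SAFTEE, but they cover most of the symptoms that the entry criteria and the disease bring. The side effects expected from light are the ones left without a baseline.

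**3. What does the between-arm comparison lose?** The protocol states no figure for SAFTEE, so there is nothing of its own to reproduce. The only documented input is 68 enrolled at 1:1, that is 68/2 = 34 per arm. This is a ceiling, since 50 are expected to finish.

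Assumptions, none from the protocol: a symptom is present at baseline in a share b and persists. Among those free of it, new onset is 20% with light and 5% with TAU.

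- Reported with light: p_L = b + (1 − b) × 0.20
- Reported with TAU: p_T = b + (1 − b) × 0.05
- Arm difference: p_L − p_T = (1 − b) × 0.15
- Share of light-arm reporters who already had the symptom: b / p_L
- Approximate power, two-sided 0.05: Φ[(difference − 1.96 × SE0) / SE1], where SE0 is the pooled and SE1 the unpooled standard error

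With a baseline, the comparison can be restricted to the 34 × (1 − b) per arm who start without the symptom, at 20% versus 5%.

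| b | p_L | p_T | Difference (points) | Already present, light arm | Power, raw, 34 per arm | Symptom-free per arm | Power, symptom-free |
|---|---|---|---|---|---|---|---|
| 10% | 28.0% | 14.5% | 13.5 | 36% | 27% | 30.6 | 42% |
| 30% | 44.0% | 33.5% | 10.5 | 68% | 14% | 23.8 | 34% |
| 50% | 60.0% | 52.5% | 7.5 | 83% | 9% | 17.0 | 26% |

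Worked line for b = 30%: SE0 = √(2 × 0.3875 × 0.6125 / 34) = 0.118 and SE1 = √[(0.44 × 0.56 + 0.335 × 0.665) / 34] = 0.117. Then (0.105 − 1.96 × 0.118) / 0.117 ≈ −1.08, which gives power of 14%.

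**4. How sensitive is the gain to spontaneous onset in TAU?** Take b = 30%, light adding 10 points of onset among the symptom-free, and about 24 symptom-free per arm.

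- No onset in TAU: 10% versus 0%, SE = √(0.10 × 0.90 / 24) = 0.061, ratio 0.10 / 0.061 = 1.6.
- 5% onset in TAU: 15% versus 5%, SE = √[(0.15 × 0.85 + 0.05 × 0.95) / 24] = 0.085, ratio 0.10 / 0.085 = 1.2.
- Raw prevalence in the first case: 37% versus 30%, SE = √[(0.37 × 0.63 + 0.30 × 0.70) / 34] = 0.114, ratio 0.07 / 0.114 = 0.6.
- Raw prevalence in the second case: 0.30 + 0.70 × 0.15 = 40.5% versus 0.30 + 0.70 × 0.05 = 33.5%, SE = √[(0.405 × 0.595 + 0.335 × 0.665) / 34] = 0.117, ratio 0.07 / 0.117 = 0.6.

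The baseline sharpens the comparison in both cases, but by less when TAU participants also develop new symptoms. In a relapsing and remitting disease some will.

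**The case against.** A reader might infer that existing symptoms and treatment effects cannot be separated at all. The documents do not support that. TAU completes the same SAFTEE on the same schedule after 1:1 randomisation, so background symptoms are balanced in expectation and the arm difference is an unbiased estimate of the effect on past-week prevalence. In the 37% versus 30% example, the 7 points are exactly 0.70 × 0.10, the share of all participants in whom light newly causes the symptom. What is lost is precision and classification of the individual. This stands.

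It is also fair that the symptoms required at entry, abdominal and bowel, are the ones best covered before treatment by other scales. Headache and eyestrain are not entry symptoms, and the protocol gives no background rate for them. This stands too, and it is why the point is confined mainly to the expected light effects.

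On purpose, the section presents SAFTEE as monitoring. Safety is not among the listed objectives, and the analysis section announces no per-arm side-effect analysis. An alert prompted by existing disease errs toward further assessment by a physician. The form's items and its threshold come from a cited study that is not at hand, so staff may ask about onset informally. These points limit the consequence. They do not supply a recorded baseline.

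Finally, the gain is modest in absolute terms. Power stays at 26% to 42% in the illustration even with a baseline, so both comparisons are underpowered. With 24 symptom-free per arm, 2 or 3 events against 0 give a two-sided Fisher p of about 0.49 or 0.23.

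**Conclusion.** The point holds in a limited form. SAFTEE has no pre-treatment administration, so symptoms that are new or worse since treatment began cannot be identified per participant on that instrument. A randomised comparison of past-week prevalence remains; it is unbiased with respect to background symptoms but diluted by them. The gap matters most for headache, eyestrain and nausea, and partly for agitation.

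The size cannot be fixed from the protocol. Under the stated assumptions (baseline prevalence 10% to 50%, full persistence, onset of 20% versus 5%, no attrition), a 15-point contrast is read as 13.5 to 7.5 points, and power at 34 per arm is 27% to 9%, against 42% to 26% among the symptom-free. The direction is dependable; the figures are illustrative.

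The primary outcome, sample size and planned models are unaffected. This is a worthwhile refinement, not a flaw that endangers the trial.

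**What to change.** Administer SAFTEE once in both arms before allocation is known, at visit 2 or at visit 3 ahead of randomisation, and add the mark to Table 3. Report by arm the items that are new or worse than that baseline, alongside the raw between-arm comparison of on-treatment reports.

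The cost is one extra questionnaire at an existing visit, with no change to the sample size. Recruitment began on February 1, 2024, so participants already past visit 3 will lack the value. The new-or-worse summary should state how many it rests on.

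The change does not make the judgement of relatedness blind, since staff will still know the arm. It gives them, and later readers, a recorded starting point.

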**Methods:**

We will recruit sixty-eight individuals with biopsy-proven IBD and clinical symptoms and randomize them to 4-weeks of morning light treatment or 4-weeks of treatment as usual (TAU), with equivalent study contact. Patient-reported outcomes (IBD-related quality of life, mood, sleep), clinician-rated disease severity, and a biomarker of gastrointestinal inflammation (fecal calprotectin) will be assessed before and after treatment. Our primary objective will be to test the effect of morning light treatment versus TAU on IBD-related quality of life and our secondary objectives will be to test the effects on clinician-rated disease activity, depression, and sleep quality. We will also explore the effect of morning light treatment versus TAU on a biomarker of gastrointestinal inflammation (fecal calprotectin), and the potential moderating effects of steroid use, restless leg syndrome, and biological sex.

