### Outcome measures

Study outcomes will be assessed in both groups at pre-treatment (visit 3) and post-treatment (visit 7). The study assessment schedule is shown **in** Table 3.

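### The depression outcome has a single post-treatment PHQ-9, and the stated missing-data remedy uses only baseline characteristics, although BDI scores are collected weekly in the same participants

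*Protocol article*

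**What the plan says.** The abstract lists depression among the secondary objectives: "our secondary objectives will be to test the effects on clinician-rated disease activity, depression, and sleep quality". The Self-reported outcomes section names the instrument: "Secondary outcome measures include the Patient Health Questionnaire-9 (PHQ-9), which is a reliable measure of the severity of depressive symptoms". The Outcome measures section fixes the times: "Study outcomes will be assessed in both groups at pre-treatment (visit 3) and post-treatment (visit 7"). Table 3 agrees, marking the PHQ-9 at visits 3 and 7.

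The BDI appears only among the safety measures. The text there places it at visits 4–7 and gives its purpose: "mood worsening will examined with the Beck Depression Inventory". Table 3 marks the BDI at visits 2, 3, 4, 5, 6 and 7.

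The Statistical power and analysis section plans 68 enrolled and 50 completers, with 25% attrition. Primary and secondary outcomes go into a random-intercept mixed model with time, group and their interaction. If more than 15% of key outcome data are missing, baseline characteristics that predict missingness become covariates. Power is stated only for the SIBDQ.

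**The concern.** With one value before and one after treatment, a participant who leaves between visits 4 and 7 adds only a visit 3 PHQ-9. The model then fills the gap, in effect, from the visit 3 score and any added baseline covariates. This is sound only if leavers and stayers with the same baseline would have had the same visit 7 score. Mood during treatment is an obvious reason why that could fail, and baseline covariates cannot capture it.

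Under Table 3, such a participant will often have left one to three BDI scores taken during treatment. The stated plan makes no use of them for the depression objective. Mood matters in this trial: it is part of the conceptual model, and the Discussion argues that benefit on mood and sleep alone would be worthwhile.

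**Working it through.** **The plan's own figures.** For the SIBDQ, 9 points / 9 points = 1.0 SD. With 25 per arm and two-sided 0.05, power is 93% (noncentral t), so the claim of at least 80% is correct. Attrition: 68 × 0.75 = 51, against the planned 50 (18/68 = 26.5% lost). The 15% trigger is 0.15 × 68 = 10.2 participants, so the expected loss exceeds it.

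**Who is affected.** Up to 18 participants would lack a visit 7 PHQ-9. Enrolment is at visit 2 and randomisation at visit 3, so some may leave before randomisation or before visit 4 and have no BDI during treatment. The documents do not give the split.

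**Bias of a baseline-only model.** Let π be the fraction missing visit 7 in an arm. Let δ be how much worse (in SD) leavers' visit 7 scores would be than those of stayers with the same baseline. Then:

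estimated benefit = true benefit + π(light) × δ(light) − π(TAU) × δ(TAU)

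Take a true benefit of 0.50 SD and π = 0.25 in each arm (both assumed):
- δ(light) = 0.24, δ(TAU) = 0: 0.50 + 0.25 × 0.24 = 0.56
- δ(light) = 0.32, δ(TAU) = 0: 0.50 + 0.25 × 0.32 = 0.58
- the same gaps in TAU only: 0.44 and 0.42
- equal gaps in both arms: 0.50, no bias

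An illustrative simulation with dropout driven by on-treatment mood gave the same 0.56 to 0.58 from a baseline-only model. Adding the BDI scores removed the bias. This holds when the recorded BDI scores explain the dropout.

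**Power, for context.** Assume 0.5 SD, 25 per arm, correlation r = 0.6 between visits 3 and 7, equal sensitivity of the two scales, and noncentral t with 48 df. None of the effect size, correlation or sensitivity is given for the PHQ-9 or BDI.
- PHQ-9 change: SD = √(2(1 − 0.6)) = 0.894; noncentrality = (0.5/0.894) × √12.5 = 1.98; power 49% (41% at r = 0.5, 61% at r = 0.7).
- BDI, mean of visits 6–7 minus mean of visits 2–3, compound symmetry: SD = √((1 − 0.6)(1/2 + 1/2)) = 0.632; power 78%. With three quarters of the effect present at visit 6, the mean effect is (0.375 + 0.5)/2 = 0.4375 SD and power is 67%.
- The same BDI contrast under AR(1), keeping r = 0.6 over four weeks: SD = 0.822; power 56%, or 45% with the rising effect.
- If no BDI is taken at visits 2–3, the visits 6–7 mean alone (compound symmetry) has SD = √((1 + 0.6)/2) = 0.894 and power 49%, the same as the PHQ-9.

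**The BDI schedule.** The Safety measures text gives visits 4–7; Table 3 gives visits 2–7. Whether a pre-randomisation BDI exists depends on which is followed.

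**The case against.** The strongest reply is that nothing here is misstated. One scale for efficacy and another for safety is a coherent choice, the trial is preliminary, and auxiliary variables often wait for an analysis plan, which is not shown. Much of this stands: no stated figure is wrong. But the article does fix a missing-data remedy, and that remedy is confined to baseline characteristics, so commenting on it is fair.

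A second reply is that the safety text may describe only monitoring after treatment starts, so it need not exclude BDI scores at visits 2–3. That is possible, but the two places should agree because the BDI baseline depends on it.

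A third is that BDI scores at visits 4–6 come from visits run by unblinded staff. Participants also know their arm, but that applies equally to the self-reported PHQ-9. The staffing point supports a supporting label; it does not prevent auxiliary use.

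A reader might go further and infer that the plan expects a medium effect on depression, tests it at coin-flip power, and could reach 61–78% by switching to the BDI. The documents do not support that. The Background says "morning light treatment improves mood (reduces nonseasonal depression) with medium effect sizes", citing meta-analyses in nonseasonal depression. Table 2 does not select participants for depression, and the plan assumes no effect size for the PHQ-9. The higher power figures need compound symmetry and pre-randomisation BDI scores; the 78% also needs the full effect by visit 6. Under AR(1) with a rising effect the BDI contrast falls to 45%, below the PHQ-9's 49%.

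**Conclusion.** The point holds as an inexpensive improvement in the handling of missing depression data. The stated remedy leaves out the only depression scores recorded between visits 3 and 7, while planned attrition exceeds the plan's own trigger. The possible bias is modest, about 0.06 to 0.08 SD on a 0.50 SD effect in the cases shown. It can go either way, and it vanishes if dropout relates to mood equally in both arms. These sizes rest on assumed dropout patterns, and the benefit of the BDI rests on its tracking the PHQ-9 well enough to explain dropout.

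No power gain should be claimed. For an assumed 0.5 SD effect at r = 0.6, the PHQ-9 test has about 49% power, and the BDI contrast at visits 6–7 ranges from about 45% to 78% depending on correlation structure and time course. Low power for a secondary outcome follows from a sample sized for 1.0 SD on the SIBDQ and contradicts nothing the plan states.

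**What to change.** 1. Reconcile the Safety measures text with Table 3 on the visits at which the BDI is completed.
2. Keep the PHQ-9 at visit 7 as the named secondary depression outcome.
3. State that available BDI scores will be auxiliary variables for a missing visit 7 PHQ-9, through a joint model or multiple imputation that allows for arm. Participants with no BDI during treatment still rely on baseline data, and this should be said.
4. Optionally, pre-specify one BDI mixed model with a named contrast (for example visits 6–7 against visits 2–3, if the earlier scores exist), labelled supporting. Naming it in advance prevents a later choice between scales.

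The cost is analysis wording plus the schedule reconciliation; under Table 3 no new visit or questionnaire is needed. The small downside of item 4 is a second depression result, collected partly at visits run by unblinded staff, which is why it should be supporting only.
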